#### Probabilistic sensitivity analysis.

Model robustness will be verified with a probabilistic sensitivity analysis using Monte Carlo simulation. For this purpose, the probability distribution functions representing the transition probabilities between states of the Markov model will be specified. Subsequently, results of model cost and effectiveness will be recalculated 10,000 times, taking random values of these distributions every time. Decision analysis, sensitivity analysis and Monte Carlo simulation will be performed with TreeAge (TreeAge Software Inc., Williamstown, Mass, USA).

### EXPECTED RESULTS

Approximately 25% of CRCs occur in first-degree relatives of patients with a history of the disease. With colonoscopy screening it is possible to detect and remove precancerous lesions (advanced adenomatous and serrated polyps) and early CRC. Currently, clinical practice guidelines recommend performing direct colonoscopy for the prevention of this neoplasia. However, compliance with this recommendation is very low, with participation rates below 50%, so now a substantial number of individuals at risk of developing the disease are unprotected. This project is innovative in that it includes a scheduled screening method with a non-invasive procedure (FIT). FIT in this study will target people with a family history of CRC, setting the index case at the heart of the screening process. This new

strategy may substantially improve adherence to screening in this population, increasing the rate of early detection of disease in the short term and resulting in a lower incidence and mortality in the long term. This project explores for the first time the efficacy of annual FIT as an alternative to colonoscopy in this high-risk population, which may represent a significant change in current clinical practice of familial CRC screening.

### RESEARCH GROUP EXPERIENCE AND SUITABILITY.

The research proposal described here seeks to continue a line of research begun in 2004 and aims to evaluate new strategies for CRC screening, led by [name] at Hospital Universitario de Canarias. This research group is part of the EPICOLON consortium, an initiative led by participating groups, including more than 25 Spanish medical centres with the aim of characterizing hereditary and familial forms of CRC in Spain. Moreover, since 2008 [name] co-directs the ColonPrev project, a multicentre study comparing screening efficacy of FIT and colonoscopy to reduce CRC mortality in the intermediate-risk population. Preliminary results of this project have been published in high impact journals (joint publications in recent years listed below).

The researchers who draft this proposal have collaborated in several projects within the EPICOLON consortium for the past ten years and already have extensive experience in the development of multicentre studies related to this issue, as evidenced by their excellent scientific production.

### WORKPLAN AND SCHEDULE. Development stages (study timeline):

**Year 1 (February 2016 to February 2017)**

- Development of study logistics (circuits, database, listings) (1^st^ quarter)
- Staff training (data-managers) (1^st^ quarter)
- Identification of index cases in Endoscopy Units
- Sending information and invitation letters to FDRs (1^st^ to 4^th^ quarter)
- Start of FDR recruitment for the study (2^nd^ to 4^th^ quarter)
- Start of colonoscopies (2^nd^ to 4^th^ quarter)
- Completion of FDR recruitment (4^th^ quarter)
- Completion of the 1^st^ screening round in the FIT group

### Year 2 (February 2017 to February 2018)

- Completion of the 2^nd^ screening round in the FIT group
- Performance of colonoscopies of randomized patients (1^st^ to 4^th^ quarter), colonoscopies of patients with positive FIT results, repetition of incomplete colonoscopies and repetition of colonoscopies in which high-risk polyps were found or where piecemeal resection of these polyps was performed.

### Year 3 (Februry 2018 to February 2019)

- Completion of the 3^rd^ screening round in the FIT group.
- Performance of colonoscopies of randomized patients (1^st^ to 4^th^ quarter), colonoscopies of patients with positive FIT results, repetition of incomplete colonoscopies and repetition of colonoscopies in which high-risk polyps were found or where piecemeal resection of these polyps was performed.
- Cost-effectiveness analysis (3^rd^ and 4^th^ quarter).

### Follow-up (February 2019 to February 2020)

Participants will be actively followed for at least 12 months after the last event registered in the study, in order to detect screening and colorectal neoplasia beyond the recruitment period. In the FIT group an interval colonoscopy is defined as any colonoscopy performed after a negative FIT result. In the colonoscopy group, interval colonoscopy refers to colonoscopies performed within 36 months after a baseline colonoscopy. Unplanned FIT is defined as any FIT performed because abdominal symptoms in both study groups or when it is performed as a screening tool in the colonoscopy group.

Screening tests, interval colonoscopies, unplanned FIT, post-polypectomy surveillance, interval CRC and deaths, will be identified through cross-linkage of the study database and the regional intranet network that provides access to the electronic medical record at each site. Interval cancer is defined as cancer occurring between 6 and 36 months after a negative screening colonoscopy.

**ParCoFit infrastructure and Allocation of tasks**

**The Scientific Committee (SC) and Scientific Advisory Board** composed by the trial local coordinators ([name]) in each Autonomous Community, will have overall responsibility and decision authority for the trial in general, including aspects of management, screening, quality control, endpoint observation and publication activity. Reviews and summarizes reports on quality and adverse events from the secretariat. They will monitor and coordinate the work of the data managers and will be responsible for checking data recorded in the online database developed for this purpose (RedCap). In addition, [name] (Canary Islands University Hospital), will be responsible for cost-effectiveness analysis.

**Coordinating secretariat.** The La Laguna secretariat manages the trial together with the national screening sites and is responsible for data collection from all screening centres. The secretariat sets up and manages the ParCoFit trial database, including tracking of data, collected and stored in REDcap hosted at the Asociación Española de Gastroenterología, a database that guarantees data confidentiality (McNicholl AG, Gisbert JP. Research to the N-Power: The Strengths of Networked Clinical Collaboration in Spain. Am J Gastroenterol. 2017;112:1761-1764).

### COMMUNICATION, DIFFUSION AND APPLICATION OF RESULTS.

Currently there are no prospective randomized clinical trials comparing different screening strategies in the high-risk familial CRC population. Completion of this clinical trial will provide evidence on the efficacy and acceptability of FIT screening in this population at high risk of CRC. This is expected to have a significant scientific impact, like that of a similar recent study on the average risk population

performed by the same research group (Quintero et al. New Engl J Med 2012). Furthermore, results of this study will be disseminated by the Oncology Group of the Spanish Oncology Association, by the EPICOLON Consortium and by the Alliance for the Prevention of CRC, entities to which researchers of this project belong. Finally, results of this study will be presented at the National Network for CRC Screening, which will evaluate the possible implementation of a new strategy for CRC prevention in the familial risk population.

### 10. AMENDMENTS Amendment 1

(Approved by the ParCoFit board on December 2, 2019)

1. Study recruitment and Study Termination

The initial Workplan (page 12) stablished that the third screened round in the FIT group and the corresponding screening colonoscopies in the one-time colonoscopy group should be completed between February 2018 and February 2019. However, the recruitment rate was much lower than expected and by December 2019 only 870 out of 1076 (81%) of the sample size had been recruited with similar screening uptake of the FIT group (439/538; 81.6%) and the colonoscopy group (431/538; 80.1%). Due to the low recruitment rate, the board decided to perform an interim analysis of the primary outcome, showing a similar screening uptake in individuals assigned to one-time colonoscopy (147/431; 34.1%) vs FIT 158/439 (35.9%) (OR 1.12; 95% CI 0.84,1.49, p=0.43).

Therefore, on December 31, 2019, when 81% of the estimated sample size was reac hed, the board decided to terminate the study prematurely after an interim analysis for futility (see page 15).

### Amendment 2

(Approved by the ParCoFit board on September 15, 2020)

As stated at the initial Workplan and Schedule (page 12), one year of follow-up (February 2019 to February 2020) was planned to collect information regarding screening uptake and colorectal neoplasia in first degree relatives beyond the recruitment period. Because of the Covid-19 pandemic the board decided on September 15, 2020 to prolong the follow-up period until December 31, 2021. Therefore, participants were actively followed from the last event registered before December 2019 until December 31, 2021. In the FIT group, an interval colonoscopy was defined as any colonoscopy performed after a negative FIT result. In the colonoscopy group, interval colonoscopy referred to colonoscopies performed within 36 months after a baseline colonoscopy. Unplanned FIT was defined as any FIT performed because of abdominal symptoms in both study groups or when it was performed as a screening tool in the colonoscopy group. Screening tests, interval colonoscopies, unplanned FIT, post-polypectomy surveillance, interval colorectal cancer, and deaths were identified through cross- linkage of the study database and the regional intranet network, which provides access to the electronic medical records at each site. Interval cancer was defined as cancer occurring between 6 and 36 months after a negative colonoscopy screening.

### Amendment 3

(Approved by the ParCoFit board on December 2, 2019)

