FIT efficacy in the familial risk population has been examined in several pilot studies, showing a sensitivity ranging from 29-80% for detection of advanced adenoma and CRC, with a specificity of 87% and 96%, respectively [14,15]. The only prospective randomized clinical trial comparing FIT and colonoscopy efficacy in FDRs of patients with CRC, conducted by our group, showed that annual FIT is equivalent to colonoscopy for the detection of advanced colorectal neoplasia according to both per- protocol analysis (OR 1.56, 95% CI 0.95, 2.56) and intention-to-treat analysis (OR 1.41, 95% CI 0.88, 2.26) [16]. However, that study was not designed to analyze screening adherence to both tests. In addition, it did not allow the authors to discern whether FIT detection of advanced colorectal neoplasia in the entire familial risk population can be extrapolated to the higher risk subpopulation. Said

subpopulation consists of FDRs of CRC index cases <60 years old and persons with two or more relatives or at least one sibling diagnosed with CRC, regardless of age at diagnosis.

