### Study groups.

GROUP 1: Screening by annual FIT for three consecutive years and colonoscopy if the FIT result is

≥10 µg of Hb/g of faeces.

GROUP 2: Screening by one-time colonoscopy. In cases where a full colonoscopy cannot be carried out, CT colonography, capsule colonoscopy or barium enema will be offered instead.

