### Selection process and screening invitation.

It will be held on a scheduled basis from index cases diagnosed of CRC during the previous 24 months at the Endoscopy Units of participating centres. After at least 3 months from diagnosis and once radiotherapy or oncologic surgery have been performed, the index case will be contacted by phone to arrange an appointment at the High Risk CRC Clinic (HRCC). In this clinic the patient will be informed of the study objectives and informed consent and permission to contact their FDRs will be requested.

If the patient agrees to participate and meets the inclusion criteria, a family tree of the first generation (parents, children or siblings) will be generated to identify all eligible and living FDRs. At this point, an open-label randomization (1:1) for the subject and investigator, to FIT for three consecutive years and work-up colonoscopy if a positive test versus straightforward colonoscopy will be performed, using the randomization module in RedCap Electronnic Data Capture (REDcap). All individuals will receive a letter signed by the medical coordinator who saw the index case in each hospital. This letter will describe the importance of CRC as a health problem in the population at familial risk and will provide information of the next study in FDRs of patients with CRC (cover letter). Later, a second letter will be sent, also signed by the medical coordinator of the study, in which the individual will be invited to participate in the randomized control study (invitation letter). The study aim and the screening option to which the individual has been assigned will also be included in this second letter. Finally, a phone number or email will be provided to request a visit to the HRCC of the corresponding hospital. Individuals who do not respond to the invitation letter after 2 months will be sent a second invitation letter.

Eligible FDRs that attend the HRCC to participate in the study will receive detailed information on the advantages and disadvantages of both tests. Participants with a negative FIT result will be sent an invitation letter to repeat the test. Crossover between groups will not be allowed.

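### Interval cancer is counted only from a negative colonoscopy, so a cancer after a negative FIT cannot carry that label and the two arms' counts are not comparable

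*Supplement*

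**What the plan says.** The Supplement defines interval cancer twice. The Follow-up section of the workplan has "Interval cancer is defined as cancer occurring between 6 and 36 months after a negative screening colonoscopy". Amendment 2, the later text, repeats the rule: "Interval cancer was defined as cancer occurring between 6 and 36 months after a negative colonoscopy screening". Neither gives a version for the FIT arm.

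Interval colonoscopy, by contrast, is defined by arm in Amendment 2. For FIT: "In the FIT group, an interval colonoscopy was defined as any colonoscopy performed after a negative FIT result". For the other arm, "interval colonoscopy referred to colonoscopies performed within 36 months after a baseline colonoscopy".

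On who has a colonoscopy in the FIT arm, Study groups specifies "Screening by annual FIT for three consecutive years and colonoscopy if the FIT result is" at or above 10 µg Hb/g faeces. Under Selection process and screening invitation, "Participants with a negative FIT result will be sent an invitation letter to repeat the test".

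On the period covered, Amendment 2 says that "participants were actively followed from the last event registered before December 2019 until December 31, 2021".

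**The concern.** An interval cancer is meant to describe a failure of the screening test: the test was negative and a cancer then appeared. In the colonoscopy arm the definition does this. In the FIT arm the typical failure is a cancer after a negative FIT, and the definition has no place for it. One label then measures different things in the two arms, and a table of interval cancers by arm would favour FIT by construction.

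This bears on interpretation, because the Background puts forward FIT as improving adherence at similar diagnostic efficiency. Interval cancer is the only named follow-up category for a cancer that screening missed.

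The interval colonoscopy rules raise a lesser problem. As worded they mix unplanned procedures with procedures that the protocol itself generates, so their rates are hard to interpret in either arm.

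**Working it through.** The plan gives no figure for this point, so the main check sets the rules side by side.

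**Interval cancer**

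| Participant | Negative protocol colonoscopy? | Can a later cancer be an interval cancer? |
|---|---|---|
| Colonoscopy arm, screened negative | Yes | Yes, at 6-36 months |
| FIT arm, FIT positive, work-up negative | Yes | Yes, at 6-36 months |
| FIT arm, all FITs negative | No | No |
| FIT arm, FIT negative, next round skipped | No | No |

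The last two rows contain the failures specific to FIT.

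**How many FIT participants fall in those rows (illustration)**

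Inputs: 158 FIT participants screened at the interim analysis (Amendment 1); three rounds (Study groups); only FIT-negative people re-invited (Selection process). Assumed, because the documents do not give them: positivity per round p = 4-15%, re-participation q = 50-100%, and every positive FIT followed by colonoscopy.

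Share ever FIT positive = p × [1 + (1−p)q + ((1−p)q)²]

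- p = 0.04, q = 1: 0.04 × 2.8816 = 0.115, or 18 of 158
- p = 0.15, q = 1: 0.15 × 2.5725 = 0.386, or 61 of 158
- p = 0.04, q = 0.5: 0.04 × 1.7104 = 0.068, or 11 of 158
- p = 0.15, q = 0.5: 0.15 × 1.6056 = 0.241, or 38 of 158

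So 97 to 147 of 158 (61-93%) would have no protocol colonoscopy. In the colonoscopy arm, all 147 people screened at that analysis were, by definition of uptake, examined by colonoscopy.

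**Interval colonoscopy, FIT arm**

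A person negative in round 1 and positive in round 2 has a work-up colonoscopy after a negative FIT, so it meets the wording. The same applies in round 3. The share of work-ups that meet it is (r2 + r3)/(r1 + r2 + r3), with r1 = p, r2 = (1−p)qp and r3 = ((1−p)q)²p. For p from 15% down to 4%:

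- q = 1: 61-65%
- q = 0.8: 53-58%
- q = 0.5: 38-42%

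Work-ups in people with no earlier negative FIT do not meet it. The FIT rule has no time limit; the colonoscopy-arm rule has 36 months.

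**Interval colonoscopy, colonoscopy arm**

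Any colonoscopy within 36 months of baseline includes the 6-12 month surveillance and the repeats of incomplete examinations described under Study variables and procedures.

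**Test sensitivity, as context only**

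The Background cites pilot studies "showing a sensitivity ranging from 29-80% for detection of advanced adenoma and CRC". One test then misses 1 − 0.80 = 20% to 1 − 0.29 = 71% of such lesions. Three completed, independent rounds miss 0.20³ = 0.8% to 0.71³ = 36%.

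**The case against.** The strongest reply is that this concerns a label in descriptive follow-up. Much of that stands, and it rules out several stronger readings that a reader might infer.

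- *Cancers missed by FIT are never recorded.* Not supported. Follow-up is meant to detect colorectal neoplasia in both arms, and linkage to medical records captures screening tests, interval colonoscopies and deaths. The fault lies in classification, not in ascertainment.
- *A key safety comparison is compromised.* Interval cancer is not among the outcomes, and neither the Statistical analysis plan section nor Amendment 3 specifies a between-arm comparison of it.
- *Screen-detected lesions drop out of the detection numerator.* Amendment 3 defines the rate as true positives over eligible subjects and removes nothing because a colonoscopy is called interval. A cancer missed in one round and found through a later positive FIT can count as a true positive.
- *FIT misses 20-71% of cancers.* The cited range covers advanced adenoma and cancer together, and applies to one test rather than three rounds.
- *Work-ups were coded as interval colonoscopies.* The documents do not show this. The workplan lists colonoscopies for positive FITs as an activity of their own, and Amendment 2 lists post-polypectomy surveillance separately. A sensible coder might keep them apart, but no rule says which label prevails.
- *Follow-up is too short.* Only people first tested by 31 December 2018 have a full 36 months by 31 December 2021. That is ordinary administrative censoring and applies to both arms.

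None of this supplies a FIT-arm definition of interval cancer. That gap is in the stated rule and remains.

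**Conclusion.** The point holds as a fault of definition. No cancer diagnosed after negative FITs alone can be an interval cancer, so the FIT-arm count is biased low and the arms are not comparable on this measure. This follows from the wording and needs no assumption, apart from setting aside negative colonoscopies done outside the protocol. The share of FIT participants affected, 61-93%, depends on the assumed positivity, re-participation and work-up completion.

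The overlap in interval colonoscopy is an ambiguity of wording; its literal extent in the FIT arm, 38-65% of work-ups, is likewise illustrative.

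The consequence is confined to follow-up reporting and to how detection results are interpreted. Screening uptake and the detection rate as defined in Amendment 3 are unaffected. With 158 FIT participants screened at the interim analysis, the number of cancers is likely to be small, so the bias matters more for what a low count is taken to mean than for any test result.

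**What to change.** 1. Start interval cancer from the arm's own negative screening test. In the FIT arm: a cancer after a negative study FIT, not detected through a later positive study FIT, within 36 months of the first FIT, and including people who skip the next round. In either arm: a cancer 6-36 months after a negative colonoscopy. Report the two components separately.
2. Exclude from interval colonoscopy those triggered by a positive study FIT, scheduled post-polypectomy surveillance, and repeats of incomplete examinations.
3. Apply the same 36-month window in both arms, with censoring at 31 December 2021.

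The cost is redrafting the definitions and recoding events that the planned record linkage already supplies; no new data collection is needed. The FIT arm may look less favourable as a result.

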### Statistical Plan Analysis (page 10)

- 1. **Multiple regression analysis**

To assess screening uptake and advanced colorectal neoplasia multivariable logistic- regression analysis was performed with adjustment for age, gender, and centre. Age was categorized as having more or less than 54 years of age, according to the median age of participants. In addition, centres were categorized as high or low recruiters, if they included

more or less than 80 eligible individuals in the study, respectively. The detection rate of advanced colorectal neoplasia was the number of subjects with true positive results divided by the number of eligible subjects.

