### Statistical analysis plan

Screening uptake and detection rate of advanced neoplasia will be assessed by intention-to-screen analysis. First-degree relatives who will not attend the initial appointment and thus do not provide information about exclusion criteria will be considered as eligible and will be included in the analysis. Non-compliers for the assigned strategy will not be allowed to change to the other group. Between- group comparisons of the main outcomes will be calculated by multivariable logistic-regression analysis with adjustment for age, gender, and centre, and results were reported as odds ratios (OR) with 95% confidence intervals.

Comparisons of continuous variables were performed using the Mann–Whitney U-test. Categorical variables with two categories were compared using the χ^2^ test. All analyses were performed using SPSS statistical software version 25.0.

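### Amendment 3 adjusts for age and centre only coarsely, through a median split and a recruiter-volume flag whose cut-points come from accrued data and should be labelled post hoc

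*Supplement*

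**What the plan says.** The section headed Statistical analysis plan compares the arms on the main outcomes by "multivariable logistic-regression analysis with adjustment for age, gender, and centre". It gives no functional form for age and no coding for centre.

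Amendment 3, under Multiple regression analysis, keeps the same three covariates for both screening uptake (primary) and advanced neoplasia, and supplies the coding. For age: "Age was categorized as having more or less than 54 years of age, according to the median age of participants". For centre: "In addition, centres were categorized as high or low recruiters, if they included" "more or less than 80 eligible individuals in the study, respectively". It gives no reason for dichotomising or for the value 80, and it plans no analysis with individual hospitals or continuous age.

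Amendment 1 reports the interim comparison by arm: "colonoscopy (147/431; 34.1%) vs FIT 158/439 (35.9%) (OR 1.12; 95% CI 0.84,1.49, p=0.43"). It does not say which model produced the odds ratio. Amendments 1 and 3 carry the same approval line: "Approved by the ParCoFit board on December 2, 2019". Amendment 3 also contains the futility result.

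**The concern.** Recruitment volume is not centre. Hospitals in the same volume class can differ in region, invitation process and baseline uptake, and a two-level flag captures none of that variation. Cutting age at the median treats everyone on one side as alike and imposes a step at 54. The model would then be described as adjusted for age and centre when it is adjusted for neither in any detail. At stake are precision and the size of the conditional odds ratio.

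The second issue is status. A median age of participants and a count of eligible individuals per hospital exist only after accrual. In an open-label trial, the only coding on paper carries the approval date of the amendment that shows uptake by arm. A reader of the report could take the model for a pre-specified one.

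**Working it through.** **Inputs.** Uptake 158/439 (FIT) and 147/431 (colonoscopy), and OR 1.12 (0.84 to 1.49), p=0.43, from Amendment 1. Hospitals: 12 in the executive summary, 11 named under Study Design. Planned size 1076, design rates 60% and 50%, 90% power, two-sided 5%, from the sample size text. Conditional power 2.95% from Amendment 3, Futility analysis.

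**1. The reported odds ratio.**
- Crude OR = (158/281)/(147/284) = 1.086.
- SE of log OR = √(1/158 + 1/281 + 1/147 + 1/284) = 0.142.
- 95% CI 0.822 to 1.435; z = 0.083/0.142 = 0.58; p = 0.56.

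The crude table does not reproduce 1.12. The reported figures agree with one another: SE = ln(1.49/0.84)/3.92 = 0.146, z = ln(1.12)/0.146 = 0.78, p = 0.44. So 1.12 is probably an adjusted estimate, but of unstated specification. The difference between 1.09 and 1.12 is at most unadjusted against adjusted. It does not compare dichotomised with full coding, which would need individual data.

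**2. The futility figure.** Information fraction t = 870/1076 = 0.809; design drift θ = 1.96 + 1.28 = 3.24. Conditional power = Φ{[z√t + θ(1−t) − 1.96]/√(1−t)}.
- Crude z = 0.58: (0.52 + 0.62 − 1.96)/0.438 = −1.87, giving 3.1%.
- z = 0.78 implied by the reported OR: 7.1%.

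The stated 2.95% is close to the crude-count value, so it appears not to depend on the age and centre coding.

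**3. How coarse the coding is.**
- 870/11 = 79.1 and 870/12 = 72.5, so the cut of 80 lies near the achieved mean per hospital.
- The flag uses 1 degree of freedom where hospital needs 10 or 11.
- If age is roughly normal and acts linearly, a median split keeps 2/π = 64% of the information on the age effect. That concerns age, not the treatment effect.

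**4. What this does to the treatment effect.** The documents give no between-hospital or age effects, so these must be assumed. Logistic simulation with 870 relatives, 11 hospitals, between-hospital SD of log-odds 0 to 1.0, age effect 0 or 0.3 per 10 years, and about 300 runs per scenario:

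| True OR | Hospital + continuous age | Flag + median split |
|---|---|---|
| 1.00, rejection rate (both codings) | no inflation (about 0.03–0.08) | no inflation (about 0.03–0.08) |
| 1.12, mean OR | 1.11–1.13 | 1.10–1.12 |
| 1.50, mean OR | 1.50–1.52 | 1.51 (SD 0) falling to 1.43 (SD 1.0) |
| 1.50, power at SD 1.0 | 0.76–0.79 | 0.70–0.71 |

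The spread in rejection rates is simulation noise.

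**5. Can the data carry the fuller model?** Uptake events: 158 + 147 = 305. Arm, age, sex and 10 or 11 hospital terms make 13 or 14 parameters, that is 305/13 = 23 or 305/14 = 22 events each. This is adequate for uptake. No event count is given for neoplasia, which must be rarer than uptake.

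**6. The absolute scale.** 158/439 − 147/431 = 0.0188; SE = √(0.360×0.640/439 + 0.341×0.659/431) = 0.0323; 95% CI −4.5 to 8.2 points. At 34.1% control uptake, a ten-point gain is (0.441/0.559)/(0.341/0.659) = OR 1.52.

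**The case against.** The best defence is that randomisation protects the comparison, so coarse covariates cannot confound it. The simulation agrees: no type I inflation, nearly identical estimates at a true odds ratio of 1.12, and a clear power loss only at a large assumed between-hospital spread. For neoplasia, pooling hospitals is an understandable answer to sparse events. The age cut is the overall participant median, a rule blind to arm and hard to tune; the recruiter flag is a hospital total over both arms, not an individual response to treatment. All of this stands and limits the size of the point. It does not make the coarser model preferable when hospital and age are already recorded.

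A reader might infer more from the documents than they support:
- **That the coding moved the odds ratio or the stopping figure.** The 1.09 and 1.12 are not the two codings, and the futility figure matches the crude counts.
- **That the cut-points were picked with the result in view.** The shared date is suggestive only. Text dated 2 December describes a decision of 31 December, so the order of interim look and coding cannot be established.
- **That Amendment 3 departs from a finer specification.** The statistical analysis plan section never fixed continuous age or hospital-level centre. The words introducing the centre sentence even leave slight doubt whether the flag stands in for hospital or is added to it.
- **That the odds ratio hides the absolute answer.** Amendment 1 gives both percentages, and the limit of 1.49 excludes the ten-point target just as the risk difference does.

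**Conclusion.** The point holds as a matter of method and labelling. Amendment 3 adjusts for age and centre only coarsely. This costs some precision and attenuates the conditional odds ratio to the extent that hospital or age effects are material; under the assumptions above, 1.5 becomes 1.43 and power falls by roughly 5 to 9 percentage points at the largest spread considered, and by little at small spreads. The trial's own hospital and age effects are unknown, so its actual loss cannot be calculated. Type I error and the null conclusion on uptake are unlikely to be affected.

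The cut-points derive from accrued data and should not be presented as pre-specified. Two smaller gaps go with this: an age of exactly 54 or a count of exactly 80 has no assigned category, and the model behind OR 1.12 is not identified.

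**What to change.** - **Uptake:** make the primary model logistic regression on arm, continuous age (linear or spline), sex and hospital, with hospital as fixed effects or a random intercept.
- **Neoplasia:** use continuous age with a random centre intercept, or penalised likelihood, because events are few.
- **Dichotomised model:** keep it as a sensitivity analysis labelled post hoc. State when and why 54 and 80 were chosen, where values equal to them fall, and whether the flag replaces hospital.
- **Reporting:** state which model gave OR 1.12 (0.84 to 1.49). Give a standardised risk difference with 95% CI beside the odds ratio; the crude interim value is 1.9 points (−4.5 to 8.2).

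The cost is a change of wording and a re-run of existing models. No new data are needed.
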